**Methods:**

In this investigator-, assessor-, and statistician-blinded parallel 2-arm randomized controlled trial, 220 adults (18+ years) with coronary heart disease are being recruited from 3 hospitals in metropolitan and regional Victoria, Australia. Participants are randomized (1:1) to receive advice to engage with usual care CR or the SCRAM intervention. SCRAM is a 24-week dual-phase intervention that includes 12 weeks of real-time remote exercise supervision and coaching from exercise physiologists, which is followed by 12 weeks of data-driven nonreal-time remote coaching via telephone. Both intervention phases include evidence- and theory-based multifactorial behavior change support delivered via smartphone push notifications. Outcomes assessed at baseline, 12 weeks, and 24 weeks include maximal aerobic exercise capacity (primary outcome at 24 weeks), modifiable cardiovascular risk factors, exercise adherence, secondary prevention self-management behaviors, health-related quality of life, and adverse events. Economic and process evaluations will determine cost-effectiveness and participant perceptions of the treatment arms, respectively.

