### Randomization

Upon completion of baseline data collection, participants are randomized at a 1:1 ratio to receive 24 weeks of usual care CR alone (control) or the 24-week SCRAM program (intervention). Treatment allocation follows a computer-generated schedule prepared by a biostatistician who is not involved in recruitment, treatment allocation, or outcome assessment; the randomization schedule is stratified by sex and trial center and uses random permuted blocks (n=2 and 4). A centralized Web-based randomization system (Research Electronic Data Capture [REDCap]; Vanderbilt University) ensures allocation concealment until the time of randomization. Access to the randomization schedule is restricted to the blinded trial biostatistician. The trial steering group is permitted access to summarized allocation progress data to monitor recruitment. Researchers undertaking data collection have no access to the randomization schedule other than to retrieve participants’ concealed treatment allocation at baseline assessments.

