### Blinding

Primary outcome assessment will be blinded; participants are blinded at baseline (ie, prerandomization) but cannot be blinded thereafter because of the nature of the treatments. A trial investigator who is not involved with data collection may be unblinded to participants’ treatment allocation if it is medically necessary. The biostatistician will remain blinded to treatment allocation throughout the analysis of trial outcomes.

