#### Intervention

Participants randomized to the intervention arm receive the 24-week SCRAM intervention. SCRAM is a multicomponent dual-phase intervention that provides participants with a comprehensive, individualized, evidence-based program of exercise training and modular behavioral self-management support via a bespoke mHealth platform. An initial 12-week intensive phase supports the uptake of exercise and CHD self-management behaviors. A subsequent 12-week maintenance phase provides lower-intensity support to help participants transition toward autonomous, long-term adherence beyond the intervention period (Figure 1). The 24-week duration is considered appropriate to observe sustained behavior change [29].

The bespoke SCRAM mHealth platform builds on our previous research [15] and includes a wearable sensor (BioHarness 3, Zephyr Performance Systems), a participant-facing app that is compatible with the Android mobile operating system (≥v5.0), and a CR professional-facing Web app that is compatible with mobile and desktop Web browsers (Figure 2). Participants access the smartphone app via a Google Play Store beta test program. Both apps have been redeveloped to ensure compatibility with recent updates to the Android mobile operating system, include improvements arising from our previous research [16], and integrate additional behavior support features.

Participants are familiarized with wearable sensor and smartphone app operation during bespoke intervention training immediately after randomization and receive an illustrated user guide. Participants also receive an induction phone call before their first scheduled exercise training session to build rapport with SCRAM exercise physiologists and reinforce operation of the technology platform. Additional technical support is provided as required throughout the trial via email and telephone.

As it is unethical to withhold evidence-based standard care, participants in the intervention arm can also self-initiate access to usual care CR, as described above. It is unclear how many participants will choose to access SCRAM and usual care CR; however, widespread low uptake of center-based CR suggests few will electively complete both programs. Self-reported usual care CR utilization will be assessed to explore the impact on trial outcomes.

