#### Primary Outcome

The primary outcome is maximal oxygen uptake (VO_2_max, mL·kg^−1^·min^−1^) measured at 24 weeks. VO_2_max is the criterion measure of maximal cardiorespiratory fitness [30], and an important clinical surrogate outcome as a 1 mL·kg^−1^·min^−1^ improvement has been associated with a 10% reduction in cardiovascular mortality among both men and women [50,51].

After a 5-min warm-up, an individualized treadmill cardiopulmonary exercise test is initiated at a self-selected velocity and 0% gradient. Thereafter, gradient is increased by 1% every 60 seconds until volitional exhaustion or indications for test termination [30]. A 5-min cooldown is completed at or below the self-selected velocity and 0% gradient. Cardiorespiratory responses are measured using a calibrated online metabolic cart; VO_2_max is defined as the mean value across 15 consecutive breaths before fatigue or symptom-limited test termination. Modification of treadmill velocity is permitted during the protocol if physiological responses indicate the self-selected velocity is insufficient to achieve an 8 to 12-min target test duration.

The individualized protocol is replicated at 24-week follow-up assessment; further modification of treadmill velocity is permitted after surpassing the baseline test duration, if required, to achieve a maximal performance.

Test procedures follow clinical guidelines, including continuous monitoring of 12-lead electrocardiogram, frequent assessment of blood pressure and patient-reported cardiovascular signs and symptoms, and medical support to administer treatment in the event of exercise-induced complications [30].

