### Data Collection and Analysis

#### Data Collection and Management

Primary outcome assessors have previous experience with cardiopulmonary exercise testing, and all outcome assessors completed standardized training for required data collection protocols/methods to ensure consistency across all 3 trial centers.

Trial data are collected and managed using REDCap tools hosted at Deakin University [53,54]. REDCap is a secure, Web-based software platform designed to support data capture for research studies. Trial data are recorded directly into REDCap case record forms or, if required, on hard copy case record forms and transcribed into REDCap as soon as possible. Data entry is conducted by outcome assessors to maintain blinding. Validation rules (eg, range and completion checks) are prespecified in REDCap to identify inaccuracies and missing data; outcome assessors respond to queries as required. Hard copy corrections (if required) are initialed and dated by outcome assessors and transcribed into REDCap as soon as possible; REDCap data logging maintains an auditable record of all electronic data entries and corrections.

Electronic data are stored on a secure password-protected server; hard copy data are stored in secure filing cabinets at trial centers until they can be transferred to the coordinating trial center. Access to trial data is restricted to members of the research team. A data manager and individuals approved by the trial steering group retain access to data from all trial centers; however, outcome assessors can only access data for their individual trial center. Unique reidentifiable codes are used to anonymize trial data. Access to identifiable data is permitted for the purposes of contacting participants, verifying data entry, analysis, auditing, or other purposes approved by the Steering Group. There are no significant or uncertain risks of harm associated with the SCRAM intervention or usual care CR, and no interim analyses are planned. Accordingly, no data safety monitoring board has been established [55].

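### Data collectors retrieve each participant's allocation at the baseline visit, so the described procedure does not secure the claimed blinding of the effort-dependent primary outcome

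*Protocol article*

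**What the plan says.** All references are to the protocol article.

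- **Randomization.** Allocation comes after the baseline measurements: "Upon completion of baseline data collection, participants are randomized at a 1:1 ratio". The web-based system "ensures allocation concealment until the time of randomization". On who may see what: "Researchers undertaking data collection have no access to the randomization schedule other than to retrieve participants’ concealed treatment allocation at baseline assessments".
- **Abstract (Methods).** The trial is introduced with the words "In this investigator-, assessor-, and statistician-blinded parallel 2-arm randomized controlled trial". The Design section makes the same claim.
- **Blinding.** "Primary outcome assessment will be blinded". The only person whom this section allows to be unblinded is an investigator with no part in data collection, and only for medical need.
- **Data Collection and Management.** "Data entry is conducted by outcome assessors to maintain blinding". Each assessor's data access is confined to one center.
- **Intervention.** "Participants are familiarized with wearable sensor and smartphone app operation during bespoke intervention training immediately after randomization".
- **Outcomes.** The baseline and 24-week visits both take place at the trial centers.
- **Primary Outcome.** The treadmill test ends at volitional exhaustion or when a termination criterion is met. At 24 weeks "further modification of treadmill velocity is permitted after surpassing the baseline test duration".

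**The concern.** The Randomization section gives the allocation to the same category of staff that the Blinding section keeps away from unblinding. Baseline data collection includes the maximal exercise test, because a participant who cannot complete it may not be randomized. Those who run exercise tests are therefore among the data collectors to whom the retrieval rule applies.

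The outcome is open to influence from the tester. How hard a participant is encouraged, whether and when the velocity is changed late in the follow-up test, and when the test is stopped can all shift the measured VO2max. Participants know their arm after randomization, so the tester's blinding is the main safeguard on how the test is conducted. Keeping the biostatistician blind protects the analysis but not the measurement.

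**Working it through.** **Step 1: set the statements side by side.**

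| Question | Randomization section | Other sections |
|---|---|---|
| Who obtains the allocation? | Researchers undertaking data collection | Blinding: unblinding is foreseen only for someone outside data collection |
| When? | At the baseline assessment, after baseline measurements | Intervention: device training follows at once |
| How long is it concealed? | Until randomization | Abstract, Design, Blinding: assessors are blind, with no time limit given |
| Who tests at 24 weeks? | Not stated | Outcomes: same centers as baseline. Data Collection: assessors are tied to one center |

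Two arrangements would reconcile the rows. The 24-week tester could always be someone other than the person who retrieved the allocation, or the allocation could be handed on unseen. The article states neither. The second also fits poorly with concealment that ends at randomization.

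**Step 2: reproduce the plan's own precision.** Inputs from Sample Size: difference 2.0 mL/kg/min, SD 6.75, r = 0.80, two-sided alpha 0.05, 90% power, 20% loss to follow-up.

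- Residual SD after baseline adjustment: 6.75 × √(1 − 0.80²) = 6.75 × 0.60 = 4.05.
- Per arm: 2 × (1.960 + 1.282)² × 4.05² / 2.0² ≈ 86.2, rounded up to 87. Total 174, which matches the plan.
- With loss to follow-up: 174 / 0.80 = 217.5, so 218. The plan's 220 is consistent with this.

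**Step 3: illustrate what a tester effect could do.** Expected completers: 220 × 0.80 = 176, or 88 per arm.

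- Standard error of the adjusted difference: 4.05 × √(2/88) = 0.611.
- With no true effect and a systematic tester-induced difference b, the two-sided type I error is P(Z > 1.96 − b/0.611) + P(Z < −1.96 − b/0.611).

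| Assumed b (mL/kg/min) | b / SE | Type I error |
|---|---|---|
| 0 | 0 | 5.0% |
| 0.25 | 0.41 | 6.9% |
| 0.5 | 0.82 | 13.0% |
| 1.0 | 1.64 | 37.4% |

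The values of b are assumptions, since the article gives no basis for any of them. For scale, 0.5 is one quarter and 1.0 is one half of the 2.0 design difference.

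**The case against.** The strongest reply is that the conflict is inferred. Retrieval happens once baseline measurements are complete, so the baseline test is unaffected. If a different person runs the 24-week test, every sentence can be true, and no sentence says the same person does both. The article also condenses a fuller protocol that is not shown, and staff rosters and database permissions are what an article commonly leaves to such a document. In addition, the test has standardising features: a calibrated metabolic cart, a 15-breath average, a replicated individual protocol, and velocity changes only once the baseline duration is passed.

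Much of this stands. Silence about rostering is no finding in itself, and the standardisation narrows the tester's discretion, although it does not remove the dependence on effort. What remains is a positive statement: the article assigns retrieval to data collectors and also claims assessor blinding, and those two statements need reconciling whatever the fuller protocol says.

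A reader might infer more than the text supports:

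- **That assessors can see all data at their center.** The Data Collection and Management section restricts access between centers. It does not say which fields an assessor sees.
- **That assessors see every past allocation and could predict the next one within blocks of 2 and 4.** The article describes retrieving individual allocations, restricts the schedule to the biostatistician, and does not say that one person makes every retrieval. Prediction of allocations would in any case be a question of selection at entry, separate from assessor blinding.

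**Conclusion.** The point holds as a conflict between a stated procedure and a headline design claim: retrieval of the allocation by data collectors does not secure blind assessment of an effort-dependent primary endpoint. It would be tempting to conclude that the trial is not assessor-blinded. The article does not support that, because it never says who conducts the 24-week tests and does not show that any of them is unblinded.

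The size of any bias cannot be derived from the article. The 7%, 13% and 37% figures are illustrative. They rest on the assumed bias sizes, on 88 completers per arm, and on the plan's SD and correlation. The sample size is not affected. This is a cheap improvement to make, and it was still useful at the time of the article: 54 of 220 participants had been randomized by September 2019, leaving 220 − 54 = 166 to enter.

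**What to change.** 1. **Randomization section.** State that REDCap releases the allocation to an existing staff member who neither assesses outcomes nor recruits, and who also arranges the device training. The SCRAM exercise physiologist team is one candidate, as it already makes an induction call to intervention participants. The research nurses are not suitable, because they identify and approach candidates.
2. **Blinding section.** State that anyone who has seen a participant's allocation may not conduct that participant's 24-week exercise test.
3. **REDCap.** Hide the allocation field from the outcome assessor's role. Assessors' access to adverse-event data need not change.
4. **Where the rule cannot be met.** Record the test as unblinded and report a sensitivity analysis of the primary outcome without those tests. Give the number of such tests by arm, because excluding them could itself unbalance the groups if they cluster in one arm.

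If the fuller protocol already separates the two roles, one sentence saying so in the Randomization section would settle the conflict.

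The cost is a change in REDCap role settings, a reassigned task, and some rostering constraint at centers with few staff. Sample size, endpoint and treatments stay as they are.

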### Blinding

Primary outcome assessment will be blinded; participants are blinded at baseline (ie, prerandomization) but cannot be blinded thereafter because of the nature of the treatments. A trial investigator who is not involved with data collection may be unblinded to participants’ treatment allocation if it is medically necessary. The biostatistician will remain blinded to treatment allocation throughout the analysis of trial outcomes.

### Treatments

#### Usual Care Cardiac Rehabilitation

All participants retain access to standard outpatient CR (ie, usual care), regardless of treatment allocation. Usual care CR typically includes face-to-face delivery of support and education to adhere to medical treatment and health-promoting lifestyle behaviors, as well as supervised exercise training. Specific program components, content, frequency, and duration vary substantially across health care providers; however, the large majority of health care providers in Australia offer education and exercise components [28].

Usual care CR is not delivered as part of this trial; as per standard clinical practice, participants are required to self-initiate engagement by requesting referral from their local health care provider.

Varied usual care CR provision is expected because of the multisite trial design. Participants who receive acute treatment at the large recruiting hospitals but live in outlying regional and rural areas will receive usual care CR via smaller regional and rural health services. Given the number of CR programs across the collective trial catchment area, it is not possible to describe all candidate programs in detail, but stratification of the treatment allocation sequence by trial center will help to balance variation across treatment groups. Participants continue to take prescribed medications and medical treatments throughout the trial period.

#### Control

Participants randomized to the control arm are advised to seek referral to usual care CR—as described above—if they wish to participate. No additional support is provided (Figure 1).

#### Intervention

Participants randomized to the intervention arm receive the 24-week SCRAM intervention. SCRAM is a multicomponent dual-phase intervention that provides participants with a comprehensive, individualized, evidence-based program of exercise training and modular behavioral self-management support via a bespoke mHealth platform. An initial 12-week intensive phase supports the uptake of exercise and CHD self-management behaviors. A subsequent 12-week maintenance phase provides lower-intensity support to help participants transition toward autonomous, long-term adherence beyond the intervention period (Figure 1). The 24-week duration is considered appropriate to observe sustained behavior change [29].

The bespoke SCRAM mHealth platform builds on our previous research [15] and includes a wearable sensor (BioHarness 3, Zephyr Performance Systems), a participant-facing app that is compatible with the Android mobile operating system (≥v5.0), and a CR professional-facing Web app that is compatible with mobile and desktop Web browsers (Figure 2). Participants access the smartphone app via a Google Play Store beta test program. Both apps have been redeveloped to ensure compatibility with recent updates to the Android mobile operating system, include improvements arising from our previous research [16], and integrate additional behavior support features.

Participants are familiarized with wearable sensor and smartphone app operation during bespoke intervention training immediately after randomization and receive an illustrated user guide. Participants also receive an induction phone call before their first scheduled exercise training session to build rapport with SCRAM exercise physiologists and reinforce operation of the technology platform. Additional technical support is provided as required throughout the trial via email and telephone.

As it is unethical to withhold evidence-based standard care, participants in the intervention arm can also self-initiate access to usual care CR, as described above. It is unclear how many participants will choose to access SCRAM and usual care CR; however, widespread low uptake of center-based CR suggests few will electively complete both programs. Self-reported usual care CR utilization will be assessed to explore the impact on trial outcomes.

**Figure 2 figure2:**
[figure not shown]
*Smartphone Cardiac Rehabilitation, Assisted self-Management* mobile health platform components.

### Intensive Phase (Weeks 1-12)

#### Exercise Training

During the initial intensive phase, real-time exercise monitoring and coaching are available during predefined operating hours (3 mornings, 06:00-10:00, plus 2 evenings 17:30-19:30 per week). At preferred times within these periods, participants self-fit the wearable sensor and activate the smartphone app to connect with remotely located exercise physiologists. Physiological (heart and respiratory rates, 1-lead electrocardiogram), geospatial (location, distance, speed—measured via Android location services), and self-reported symptom data (if any) are transmitted to a cloud server and visualized in the Web app for review by exercise physiologists, all in real time. Participants receive real-time individualized coaching, feedback, and support from exercise physiologists—based on exercise performance data—throughout exercise training via smartphone app text-to-voice audio notifications. Outside of predefined operating hours, participants use the smartphone app to self-monitor their exercise performance (in real time during exercise and retrospectively after exercise—using automated graphing elements); set exercise goals and review goal achievement feedback (via automated graphing elements); and receive evidence- and theory-based behavioral support via push notifications (see below).

During operating hours, exercise physiologists use the Web app to monitor participants’ location, distance, speed, heart and respiratory rates, electrocardiogram, and self-reported cardiac symptoms (if any), as well as provide participants with regular real-time coaching instruction, feedback, and support during exercise. Coaching interactions are delivered to participants via a text-to-voice protocol. Exercise physiologists also retrospectively review participants’ exercise performance and goal achievement data via the Web app to inform individualized and progressive exercise prescription, and they may contact participants via telephone and email to discuss program progression if required. Collectively, these features enable optimal individualization and progression of participants’ exercise prescription throughout the 12-week intensive phase.

Exercise physiologists received initial training to apply their expertise via the SCRAM platform, and they receive ad hoc support to maintain intervention fidelity and quality throughout the trial.

The SCRAM platform supports simultaneous monitoring of multiple participants, and the use of mobile and Web apps allows participants and exercise physiologists to operate in any environment with an active Wi-Fi or third/fourth generation cellular broadband connection; data use is typically less than 5 MB per participant, per hour of exercise training [15]. This level of oversight is similar to center-based programs and a significant improvement on existing home-based CR.

Following American College of Sports Medicine guidelines [30], exercise physiologists provide individualized exercise prescription based on participants’ clinical status, exercise capacity, exercise-induced cardiac signs and symptoms (if any), age, sex, and personal preferences. Exercise frequency, duration, and intensity-level targets are delivered to participants via the smartphone app. Initial prescription targets 3 sessions per week of 30 to 40-min duration at 40% to 50% heart rate reserve (HRR). Exercise prescription parameters are progressively increased according to participants’ exercise tolerance, signs and symptoms, and clinical status, targeting 3 to 5 weekly sessions of 60 min at 65% to 85% HRR by the end of the 12-week intensive phase. Prescribed exercise intensity levels are sufficient to induce physiological adaptation without inducing abnormal clinical signs or symptoms. All exercise training sessions include warm-up and cooldown periods to enable appropriate cardiovascular and musculoskeletal preparation and recovery. Walking is the preferred exercise mode, as it does not require specific equipment; however, participants can choose other land-based modes if preferred.

